**Significance:**

Our expected result is that the developed model of severe influenza can be more accurate and have a lower misdiagnosis rate than traditional clinical assessment. The pre-specified AUC was 0.18 (95% CI: 0.14-0.22), with an expected 32% reduction in misdiagnosis. The model’s performance was consistent across patients in older adults, underlying disease, and resource-poor areas. The added value of the study is that it is effective in improving early recognition of severe influenza.

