## Introduction

1

Influenza causes 650,000 deaths annually and remains a threat to global health. Influenza has a mortality rate of approximately 20 per cent, and deaths due to influenza predominantly occur among infants, pregnant women, the elderly and the immunocompromised (1, 2). Although progress has been made with previously developed predictive tools and antiviral therapies, this has not reduced mortality from severe influenza (3). A key issue is the dynamic gap between clinical decision-making and risk of severe influenza. Evidence suggests that physicians are overconfident in the outcome of subjective clinical assessments leading to misdiagnosis and quality delays in severe influenza. Another factor, of course, arises from differences in the definition of ‘cure’ in the healthcare system (4, 5). A study by Valenzuela-Sánchez et al. (2024) reported that 34% of severe influenza cases were initially incorrectly classified as mild. The reason for this was an over-reliance on non-specific symptoms by clinicians when assessing influenza (6). This result implies that we need more objective and accurate tools to improve the accuracy of clinical judgement.

Artificial Intelligence (AI) can learn deeply from human health data so that closed-source predictive models can be constructed to identify high-risk patients. The current intersection of AI and healthcare data has shown revolutionary potential (7, 8). Yang et al. (2023) developed an influenza prognostic AI model using only city-scale data, which has achieved a performance AUC value of 0.89 (9). Of course, the lack of external validation of models constructed using AI across regions and healthcare resources means that more effort is needed for AI to address real-world clinical work (10). Dai et al. (2024) concluded that constructed AI diagnostic tools do not work well when put into prospective clinical practice due to population heterogeneity and data drift (11). This may be due to the lack of research-oriented personnel in the field of AI, leaving little understanding of dynamic risk prediction in high-risk subgroups in a clinical context (12).

The aim of our research is to develop and validate a deep learning-based diagnostic model for severe influenza. In order to be able to specify the research tasks at each stage, we established a methodological framework.

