Data: data were obtained from 87 hospitals in Jiangsu Province, China. The data features of interest were clinical information, laboratory test results, and demographic information.Stages: 5 research phases with model building, internal validation, comparative study, randomised trial, and prospective real-world validation.Collaboration: the aim of the model is to assist clinicians in accurately identifying patients with severe influenza.

We hypothesize that this model will significantly improve AUC (*Δ* > 0.15) compared to physician-only assessments, reduce misdiagnosis rates by ≥30%, and maintain robustness across hospitals with varying resource levels. By addressing both algorithmic and human factors, this research seeks to establish a scalable solution for mitigating influenza-related mortality, particularly in resource-constrained settings.

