#### Phase III: multi-reader, multi-case validation

2.3.3

Phase 3 used a two-round diagnostic design for evaluating the impact of AI model assistance on the effectiveness of clinician decision-making. The AI models used in Phase 3 were calibrated in the Phase 2 validation phase. Recruited clinicians are split into two rounds subsequently evaluating cases independently then filling in the diagnosis.

The first round of tasks that clinicians receive is the baseline diagnostic assessment. In the baseline diagnostic assessment, clinicians are required to evaluate cases using a standard influenza diagnostic protocol and subsequently complete the diagnostic results.

The second round of tasks allows clinicians to access the risk scores and key influencing factor scores generated by the AI model to fill in the diagnosis during the evaluation of the case.

All clinicians were required to undergo two rounds of tasks. This was done with reference to a previous study (22). The use of machine-assisted diagnosis by clinicians can increase their productivity (23). To minimise bias, cases are randomly reordered between rounds of assessment and a 4-week washout period is set between assessments to reduce recall effects. Diagnostic accuracy (measured as AUC) and clinician confidence (scored on a 5-point Likert scale) will be compared between rounds of assessment to quantify the impact of the model on decision consistency and clinician certainty. This multi-reader, multi-case framework ensures robust assessment of AI-human collaboration while addressing variations in real-world clinical work.

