#### Phase V: prospective validation study

2.3.5

As Dai et al. illustrate the point, using prospective cohort data validation provides a better view of the model’s performance in the real world (24). This final phase evaluates the model’s real-world clinical utility during the 2025 influenza season. The AI model will be deployed in real time to analyze EHRs of newly admitted influenza patients across all 87 hospitals. Clinicians will receive model-generated predictions (such as risk scores, key contributing factors) within 2 h of case entry via a secure, institution-specific dashboard.

Data collection will capture:

Clinician actions: Initial diagnosis (pre-model assessment), final diagnosis (post-model review), and time-to-decision (minutes from case entry to diagnosis).Model performance: Concordance between model predictions and ground truth (severe influenza confirmed by an independent adjudication panel).

This prospective design validates the model’s operational feasibility, diagnostic timeliness, and accuracy in dynamic clinical environments, providing critical evidence for scalability and regulatory approval.

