#### Secondary outcomes analysis

2.8.2

Secondary endpoints include diagnostic sensitivity and specificity, calculated using the Clopper-Pearson exact method for binomial proportions to determine the model’s and clinicians’ ability to correctly identify true positive and true negative cases, respectively. Differences between clinician and model performance will be assessed via the Mann–Whitney U test, a non-parametric method suitable for skewed distributions. Positive and negative predictive values (PPV/NPV) will be adjusted for influenza prevalence using Bayes’ theorem and reported with 95% confidence intervals to reflect their clinical utility in real-world settings. The misdiagnosis rate, defined as the sum of false positives and false negatives per 100 diagnoses, will be analyzed using an independent samples t-test (if normally distributed) or Wilcoxon rank-sum test (for non-normal data), quantifying the model’s impact on reducing diagnostic errors. These metrics collectively evaluate the model’s precision, reliability, and practical value in augmenting clinical decision-making.

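### The misdiagnosis rate is given a normality-gated independent-samples test with no unit or phase fixed; it ignores pairing where cases are shared and is not tied to the 30% hypothesis

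*Protocol article*

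**What the plan says.** Section 2.8.2 (Secondary outcomes analysis) of the protocol article treats the misdiagnosis rate as an error count, "defined as the sum of false positives and false negatives per 100 diagnoses", and says it "will be analyzed using an independent samples t-test (if normally distributed) or Wilcoxon rank-sum test (for non-normal data"). For accuracy measures the same section says "Differences between clinician and model performance will be assessed via the Mann–Whitney U test". It names no phase, no unit (diagnosis, clinician or hospital), no clustering adjustment and no relative-effect estimate for this endpoint.

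The phases differ in structure:

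- **Phase III (2.3.3):** "All clinicians were required to undergo two rounds of tasks", on cases that are reordered between rounds after a washout.
- **Phase IV (2.3.4):** clinicians are randomised 1:1 to assisted or unassisted diagnosis.
- **Phase V (2.3.5):** the data for each case include "Initial diagnosis (pre-model assessment), final diagnosis (post-model review").

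The target is relative. The Introduction hypothesises that the model will "reduce misdiagnosis rates by ≥30" per cent, and the abstract speaks of the model "with an expected 32% reduction in misdiagnosis". For AUC the plan already uses the Dorfman-Berbaum-Metz (DBM) method to allow for readers and cases (2.4.1, 2.8.1). Section 2.5.2 acknowledges hospital-level clustering when setting the number of clinicians.

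**The concern.** The plan names one kind of test for an endpoint that arises in designs needing different analyses. An independent-samples test suits two separate groups. It does not suit two diagnoses of one case by one clinician, or a clinician and a model scored on the same cases.

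In Phase IV the validity of the test depends on a unit that the text leaves open. Choosing between t-test and rank test by a normality check also lets the data decide what is reported, and the rank test reports no percentage reduction. At stake are the power of the paired comparisons and the ability to say whether the reduction in misdiagnosis reached the hypothesised 30%.

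**Working it through.** The plan gives no power or sample-size figure for this endpoint, so there is none to reproduce. The checks below use its structure and numbers, with assumptions marked.

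**1. Pairing.** With equal variances σ², n pairs and within-pair correlation ρ, the variance of a difference in means is 2σ²/n if pairing is ignored and 2σ²(1−ρ)/n if it is used. The ratio of standard errors is 1/√(1−ρ). The values of ρ are assumed.

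| ρ | 1/√(1−ρ) | SE too large by |
|---|---|---|
| 0.3 | 1/√0.7 = 1.20 | 20% |
| 0.5 | 1/√0.5 = 1.41 | 41% |
| 0.7 | 1/√0.3 = 1.83 | 83% |

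At ρ = 0.5 the variance doubles, which equals discarding half the pairs. A simulation of two-round data (assumed: 60 readers, 10 or 20 cases each, 34% error, intraclass correlation (ICC) 0.05 to 0.20) gave the independent t-test a type I error of 0 to 1.3%. Its power for a 15% relative reduction was 6 to 51%, against 49 to 82% for a paired t-test on the same data.

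**2. Phase IV, by unit of analysis.** Simulation under no effect, 109 clinicians per arm (section 2.5.2), error rate 34%, ICC 0.01 to 0.10 (assumed):

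| Diagnoses per clinician | Type I error, t-test on single diagnoses |
|---|---|
| 2 | 5.5 to 5.9% |
| 10 | 6.3 to 15.8% |
| 20 | 7.2 to 24.5% |

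An independent t-test on one rate per clinician stayed at 4.4 to 5.4% across 2 to 20 diagnoses per clinician. The design effect 1 + (m−1)×ICC explains the pattern: at ICC 0.10 it is 1.1 for m = 2 and 2.9 for m = 20. Hospital-level clustering was not simulated.

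**3. Which branch the normality check selects.** If all 348 patients were Phase IV cases read once by 218 clinicians, each would make 348/218 = 1.6 diagnoses, so most rates would be 0, 50 or 100 per 100. In the simulation a Shapiro-Wilk check never passed in both arms at 2, 5 or 10 diagnoses per clinician. It passed in 3 to 12% of runs at 20. Wilcoxon would nearly always be used.

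**4. What the hypothesis needs.** Take a control error rate of 34% and a true 30% reduction: 0.34 × 0.70 = 0.238. With 174 per group and no clustering:

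- SE of ln RR = √[0.66/(0.34×174) + 0.762/(0.238×174)] = √(0.01116 + 0.01840) = 0.172
- 95% CI = exp(−0.357 ± 1.96×0.172) = 0.50 to 0.98

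The same formula gives 0.44 to 1.12 at a 20% control rate and 0.52 to 0.94 at 40%. The 34% is a stand-in. The Introduction reports that "34% of severe influenza cases were initially incorrectly classified as mild", which is a miss rate among severe cases and not false positives plus false negatives over all diagnoses.

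**5. Binary data alone.** For 59/174 against 41/174 errors, the t-test and the chi-square test both give p = 0.033. The risk ratio for these counts is 0.69 (95% CI 0.50 to 0.97), which neither test named in the plan reports.

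**The case against.** The best defence is that the named test fits the two-arm Phase IV and was meant for it. Section 2.8.2 assigns it to no other phase. The between-round comparisons listed for Phase III are AUC and confidence, not misdiagnosis, and Phase V names no test. Mapping a secondary endpoint to phases is often left to an analysis plan. This stands in part: the pairing criticism applies only if the test is used on Phases III and V, or on clinician versus model with shared cases. But the protocol has already fixed the method without restriction, and it says nothing else about how misdiagnosis would be compared there.

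A reader might also infer several stronger points that the documents do not support:

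- **The Phase IV error rate is wrong.** Not shown. A two-sample test on one rate per clinician is a recognised cluster-level analysis and held its size. At about 2 diagnoses per clinician even a diagnosis-level test is close to nominal for clinician clustering. Marked inflation needs 10 to 20 diagnoses each, and the plan does not give that number.
- **A t-test is invalid for binary data.** At this sample size it agrees with the chi-square test.
- **The plan cannot estimate the reduction.** True only of the Wilcoxon statistic. The t-test yields two mean rates, from which a relative reduction follows, and nothing forbids reporting one.
- **Ignoring the pairing creates false positives.** With positive correlation it does the opposite and makes the test conservative.

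**Conclusion.** The point holds in a limited form. Section 2.8.2 fixes a normality-gated independent-samples test without unit or phase. Where cases are shared, that test discards the pairing and costs power, with standard errors 20 to 83% too large over the assumed correlations of 0.3 to 0.7. In Phase IV it is valid on clinician-level rates. On single diagnoses it ignores clustering by clinician and hospital, and the size of that error depends on the number of diagnoses per clinician. The branch most likely to be chosen gives no relative reduction with an interval to compare with the hypothesised 30%.

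The baseline error rate, ICCs, within-pair correlations, number of readers and diagnoses per clinician are all assumptions. The 1.6 diagnoses per clinician and the 174 per group further assume that all 348 patients are Phase IV cases read once, whereas section 2.5.3 spreads them over retrospective and prospective cohorts. This is a secondary endpoint but a stated hypothesis, so the wording should be corrected.

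**What to change.** Remove the choice by normality check, and state unit and phase for each comparison.

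- **Phase IV:** fit a binary model per diagnosis, for example modified Poisson GEE. Account for clustering by clinician and by hospital as the higher level, with the stratification factors (hospital tier and experience level) as covariates. Report the risk ratio with 95% CI and judge it against 0.70, saying in advance whether the point estimate or the upper limit must meet that value.
- **Phase V:** use a paired analysis of the pre-model and post-model diagnoses of each case, allowing for clinician and hospital.
- **Phase III:** use a paired analysis that accounts for both reader and case, such as crossed random effects or a multi-reader multi-case method for binary outcomes, in line with the DBM approach already planned for AUC. Clustering by clinician alone would leave the correlation from shared cases unhandled.
- **Clinician versus model on the same cases:** replace Mann-Whitney with a paired method.

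The cost is analysis wording and code; no extra data are needed.

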#### Subgroup analyses

2.8.3

Subgroup analyses will evaluate the model’s performance heterogeneity across predefined categories: patient-level factors (age [infants, children, adults, older adults], comorbidities, and vaccination status), clinician-level factors (experience [resident, attending, chief] and hospital resource tier [urban vs. rural]), and geographic variation (northern vs. southern Jiangsu Province). To mitigate bias, statistical adjustments include Bonferroni correction for multiple comparisons (adjusted *α* = 0.05 / number of subgroups) and multivariable logistic regression controlling for confounders such as seasonal trends, baseline viral load, and treatment delays. These analyses aim to identify subgroups where the model excels or underperforms, ensuring tailored clinical deployment and validating robustness across diverse healthcare settings.

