#### Subgroup analyses

2.4.3

Predefined subgroup analyses will assess heterogeneity in model performance across key variables to evaluate the impact of local healthcare infrastructure and influenza epidemiology.

patient characteristics: age (infants, children, adults, older adults), comorbidities (cardiovascular disease, diabetes), and vaccination status (yes, no);clinician factors: experience level (resident, attending, chief physician);hospital resource tier: urban or rural facilities;geographic variation: northern or southern regions of Jiangsu Province.

These analyses aim to identify subgroups where the model excels or underperforms, informing targeted clinical deployment. Statistical adjustments, such as Bonferroni correction for multiple comparisons and multivariable regression for confounders, will ensure robust interpretation of subgroup differences.

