#### Intervention groups

2.6.3

In the control group, clinicians (without any AI assistance) will diagnose influenza cases using standard clinical protocols, integrating symptoms, laboratory results, and imaging findings. Patients in this group will receive routine care based solely on clinician assessments.

In contrast, the model-assisted group will utilize a secure digital dashboard providing real-time AI predictions, including a risk score (0–100%) for severe influenza progression and highlighted contributing factors (such as prolonged fever duration, abnormal lymphocyte counts).

While the model offers data-driven insights, its outputs are non-prescriptive; clinicians retain full authority to accept, modify, or reject recommendations, ensuring clinical judgment remains central to decision-making. This design balances technological support with practitioner autonomy, reflecting real-world diagnostic workflows.

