#### Primary outcome analysis

2.8.1

The AUC will serve as the primary metric to evaluate the diagnostic accuracy of the AI model. To account for variability inherent in multi-reader, multi-case study designs, the DBM method will be employed, which adjusts for differences in clinician interpretations and case complexity. Analyses will be conducted using the MRMCaov (v0.2.1) and pROC (v1.18.0) packages in R, generating AUC values with 95% confidence intervals (CIs) derived from non-parametric bootstrapping (1,000 iterations). A clinically significant improvement is predefined as a ΔAUC more than 0.15 between the model-assisted and control groups, with the null hypothesis assuming no discriminative capacity (AUC less than 0.70, equivalent to random guessing). This approach ensures robust statistical inference while addressing real-world diagnostic variability across clinicians and settings. Hyperparameter optimization was conducted via Bayesian optimization with 5-fold cross-validation, prioritizing AUC on the validation set.

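### The subgroup target is worded as the model's own performance, which for clinician experience would show only case mix; it should be the assisted-minus-unassisted difference

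*Protocol article*

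**What the plan says.** Two sections of the protocol article set the target of the subgroup analyses. Section 2.4.3 states: "Predefined subgroup analyses will assess heterogeneity in model performance across key variables". Section 2.8.3 says they will "evaluate the model’s performance heterogeneity across predefined categories" and gives the purpose: "These analyses aim to identify subgroups where the model excels or underperforms". Both include clinician experience; in section 2.8.3 the entry reads "clinician-level factors (experience [resident, attending, chief] and hospital resource tier [urban vs. rural". Section 2.8.3 adds a Bonferroni divisor equal to the number of subgroups and a multivariable logistic regression for confounders.

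The primary comparison is of a different kind. Section 2.8.1 defines it as a "ΔAUC more than 0.15 between the model-assisted and control groups", that is, a contrast between two groups of clinicians. Under section 2.6.3, "clinicians retain full authority to accept, modify, or reject recommendations", so what assistance achieves depends on the reader as well as on the score.

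**The concern.** The model computes its risk score from the patient record. If model performance means that score against the true outcome, the clinician's seniority does not enter the calculation, yet seniority is one of the listed subgroup factors. A comparison of model AUC across experience levels could then mislead in two ways. It could show no heterogeneity while assistance helps juniors much more than seniors. It could also show heterogeneity only because seniors see harder patients.

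At stake is the purpose given in section 2.8.3, which is to fit deployment to the setting. Where to deploy a tool that clinicians may override depends on where it improves their decisions, and model AUC by experience level does not measure that.

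**Working it through.** **1. The two uses of the term, side by side.**

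- *Stand-alone sense.* Section 2.3.5 (Phase V) has "Model performance: Concordance between model predictions and ground truth" as one item of data collection and clinician actions as another. Section 2.8.2 likewise contrasts clinician with model performance.
- *Assisted-versus-control sense.* Section 2.3.2 (Phase II) uses the comparison of clinicians with and without AI, including their diagnosis time, to evaluate the AI model. Sections 2.4.1 and 2.8.1 introduce AUC as a property of the model and then judge it by the difference between the experimental and control groups.

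Sections 2.4.3 and 2.8.3 do not say which sense applies, and neither names the assisted-minus-control difference.

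**2. What the literal sense gives for experience.** If all levels read the same cases, model AUC is identical across levels by construction. If they see different patients, it can differ only through case mix. Adjusting for confounders can at most remove that difference; it cannot turn it into an effect of assistance.

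A simulation shows the consequence. Assumed: 348 cases, 30% severe, 300 repetitions, unaided accuracy rising with seniority, and assisted reading modelled as a combination of the clinician's and the model's information.

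| Level | Model AUC | Unaided AUC | Assisted AUC | Gain |
|---|---|---|---|---|
| Resident | 0.853 | 0.638 | 0.866 | 0.23 |
| Attending | 0.853 | 0.703 | 0.880 | 0.18 |
| Chief | 0.853 | 0.801 | 0.910 | 0.11 |

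The equal model AUCs are built in, because that is what the literal definition implies. The gains depend on the assumed values and are not a forecast.

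**3. What the design can estimate.** In Phase III (section 2.3.3) every clinician reads without and then with the model. In Phase IV (sections 2.3.4 and 2.6.1) clinicians are randomised 1:1 within strata of experience and hospital tier. Both allow an assisted-minus-unassisted difference by experience level.

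**4. How precise that would be in Phase IV.** Inputs from sections 2.5.1 and 2.5.2: AUC 0.85 and 0.70, two-sided alpha 0.05, 174 patients per group. Assumed: an equal three-way split by experience and no clustering.

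The plan's own figure first. Its formula with its inputs gives (1.96 + 1.645)² × 0.3375 / 0.15² = 194.9, so 195 per group, not the 145 stated; 174 is 145 × 1.2. That is a separate matter. The stated 174 is used below only to show precision at the planned size.

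- Variance term: 0.85 × 0.15 + 0.70 × 0.30 = 0.3375
- Patients per arm per level: 174 / 3 = 58
- SE of the AUC difference within a level: √(0.3375 / 58) = 0.076
- 95% half-width: 1.96 × 0.0763 = 0.15
- Power for a difference of 0.15 within a level: Φ(0.15 / 0.0763 − 1.96) ≈ 50%
- SE of the difference in gain between two levels: 0.0763 × √2 = 0.108
- Power for a 0.15 difference in gain: Φ(0.15 / 0.1079 − 1.96) = Φ(−0.57) ≈ 28%
- The same at alpha 0.05/7 (one test per factor, seven factors): Φ(1.39 − 2.69) ≈ 10%

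With 145 per group (48 per arm per level) the SE is 0.084, the half-width 0.16 and the power for a 0.15 difference in gain 24%.

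**The case against.** The strongest reply is that the authors mean the assisted comparison throughout. Section 2.3.2 groups clinicians by seniority, compares them with and without AI, and calls the result an evaluation of the AI model. Sections 2.4.1 and 2.8.1 do much the same. Listing clinician experience as a subgroup factor makes sense only on that reading. This stands as a plausible account of intent. It does not settle the text, because section 2.3.5 uses the term in the other sense and the two senses lead to different analyses.

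A second reply is that the form of an interaction test belongs in an analysis plan that is not shown. That is right as far as a missing test goes. The point here concerns the target that the article does state, which an analysis plan following it would carry forward.

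A reader might go further and infer that the trial cannot say for whom assistance helps, or that the subgroup plan as a whole has no content. The documents support neither. The paired Phase III reads and the stratified Phase IV randomisation keep the effect of assistance by level estimable. Only the experience factor loses its meaning on the literal reading: stand-alone model AUC by age, comorbidity, vaccination status, hospital tier and region remains a legitimate question.

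**Conclusion.** The subgroup target is inconsistently defined. Read literally, it does not match the primary contrast and makes the experience comparison a display of case mix. This is a fault in the stated target, not in the design, and it is confined to one factor as regards loss of meaning. The reasoning on that factor needs no numerical assumption beyond the score being computed from the patient record.

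The corrected analysis would be imprecise: about ±0.15 per experience level, and about 28% power for a 0.15 difference in gain between two levels before any multiplicity correction. These figures rest on the article's variance formula, an equal three-way split of 174 per arm and no clustering. They apply to the unpaired Phase IV comparison. Clustering of cases within clinicians would normally widen the intervals, as would a share of the 348 patients coming from the retrospective cohort, which section 2.5.3 allows. The subgroup results can therefore be exploratory only.

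**What to change.** In sections 2.4.3 and 2.8.3:

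- For Phases III and IV, define the subgroup effect as the assisted-minus-unassisted difference in clinician AUC within each level, with its 95% CI.
- Test heterogeneity with one assistance-by-factor interaction per factor, and count factors in the multiplicity correction. With cardiovascular disease and diabetes taken separately there are seven: age, cardiovascular disease, diabetes, vaccination, experience, tier and region.
- Report stand-alone model AUC under its own label, for patient, hospital-tier and region factors only.
- Label the subgroup results exploratory and give their expected precision.

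The cost is a few sentences and an interaction term; the reads and the randomisation strata are already in the design. The drawback is that the interaction estimates will be wide, so a non-significant result must not be reported as evidence that assistance works equally well at every level.

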#### Hospital inclusion criteria

2.1.1

We have pre-set criteria for hospital eligibility for the study. Hospitals must be accredited tertiary general hospitals, which provide full emergency and inpatient services. Hospitals should have at least 100 patients with influenza diagnosed by laboratory testing between 2021 and 2023. Hospital clinicians must use electronic health records (EHRs) so that symptoms of influenza patients and other information used for clinical research can be recorded in a standardised format. Longitudinal, anonymous data sharing programmes must be in place within hospitals to ensure the security of patient and clinician information.

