#### Sample size derivation

2.5.2

The sample size calculation began with an initial estimate of 145 patients per group (290 total), derived from a power analysis targeting a clinically significant ΔAUC of 0.15 (*α* = 0.05, *β* = 0.95). To account for potential 20% attrition due to incomplete data or participant dropout, the final patient sample was adjusted to 174 per group (348 total). For clinicians, a minimum of 218 participants (109 per group) was required to ensure balanced representation across experience levels (resident, attending, chief) while addressing hospital-level clustering effects, as recommended by methodology for cluster-randomized trials (35). This dual-tiered approach balances statistical precision with pragmatic considerations, ensuring robust evaluation of the AI model’s impact in diverse clinical environments.

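### Section 2.8.3 names a logistic regression with no clinician or hospital term for subgroup factors that are fixed within a clinician or hospital, so fitted as named it would not hold the Bonferroni level

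*Protocol article*

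**What the plan says.** Section 2.8.3 states its purpose as follows: "Subgroup analyses will evaluate the model’s performance heterogeneity across predefined categories". Besides patient factors, it lists "clinician-level factors (experience [resident, attending, chief] and hospital resource tier [urban vs. rural"], and then northern versus southern Jiangsu. Two adjustments are named. The first deals with multiplicity: "Bonferroni correction for multiple comparisons (adjusted *α* = 0.05 / number of subgroups"). The second is a regression model, given in these words: "multivariable logistic regression controlling for confounders such as seasonal trends, baseline viral load, and treatment delays". The outcome of the regression is not named, and the text does not say outright that the regression is the subgroup test.

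Correlation is recognised in two other places. Section 2.8.1 says of the primary AUC: "To account for variability inherent in multi-reader, multi-case study designs, the DBM method will be employed". Section 2.5.2 says of clinicians that "a minimum of 218 participants (109 per group) was required" to balance experience levels, "while addressing hospital-level clustering effects, as recommended by methodology for cluster-randomized trials". No ICC, design effect or number of cases per clinician is given anywhere.

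**The concern.** For a factor that does not vary within a cluster, the independent information comes from the clusters: 218 clinicians for experience, 87 hospitals for tier and region. A logistic regression with only patient-level and seasonal covariates counts each diagnosis as a separate piece of evidence on these factors. If diagnoses from one clinician or hospital resemble each other, the standard errors are too small. Bonferroni lowers the threshold, but it cannot repair p-values that are themselves too small.

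At stake is the use made of these results. Section 2.8.3 says that they will identify where the model does well or badly and guide deployment. The introduction makes robustness across hospitals of different resource levels part of the hypothesis. Chance variation between hospitals could be reported as an urban/rural or regional effect.

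**Working it through.** **No figure to reproduce.** The article states no numeric subgroup alpha, ICC or design effect, so the check asks how far the level would be exceeded over a range of assumptions.

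**Inputs from the article**
- 348 patients (2.5.3), 218 clinicians (2.5.2), 87 hospitals (2.1).
- Averages: 348/87 = 4 patients per hospital; 348/218 = 1.6 patients per clinician.
- Hospital eligibility (2.1.1): "Hospitals should have at least 100 patients with influenza diagnosed by laboratory testing between 2021 and 2023", or 100/3, about 33 per year. This is an entry threshold and not an analysis sample; it serves only as a scale for Phase V, which covers newly admitted patients at all 87 hospitals.

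**Assumptions**
- ICC 0.01-0.20.
- 10-50 reads per clinician in the reader phases.
- K = 6 subgroup factors (age, comorbidity, vaccination, experience, tier, region), so alpha = 0.05/6 = 0.0083. The article gives no K. Counting cardiovascular disease and diabetes separately gives 7; counting levels gives about 15 (0.0033).

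**Formula.** With m diagnoses per cluster, DE = 1 + (m - 1) x ICC. The actual size of a test that ignores clustering is 2 x [1 - Phi(z / sqrt(DE))], where z is the nominal two-sided critical value.

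| m per cluster | ICC | DE | Size at nominal 0.0083 | Ratio |
|---|---|---|---|---|
| 1.6 (clinician, stated average) | 0.05 | 1.03 | 0.0093 | 1.1 |
| 1.6 | 0.10 | 1.06 | 0.0104 | 1.2 |
| 4 (hospital, stated average) | 0.05 | 1.15 | 0.0139 | 1.7 |
| 4 | 0.10 | 1.30 | 0.0207 | 2.5 |
| 10 (assumed) | 0.05 | 1.45 | 0.0285 | 3.4 |
| 20 (assumed) | 0.05 | 1.95 | 0.0589 | 7.1 |
| 50 (assumed) | 0.05 | 3.45 | 0.1555 | 18.7 |

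**Family-wise error at the stated averages.** Three of six tests are affected: experience at m = 1.6, tier and region at m = 4.
- ICC 0.05: 1 - (1 - 0.0083)^3 x (1 - 0.0093) x (1 - 0.0139)^2, about 0.061.
- ICC 0.10: the same with 0.0104 and 0.0207, about 0.074.
- The target is 0.05.

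**Simulation.** The formula overstates the effect somewhat when the ICC is defined on the logit scale. Simulating a two-level cluster-constant factor with no true effect and a random cluster intercept gives, at nominal 5%:
- 87 hospitals x 4 patients: about 6-7% at ICC 0.05-0.10.
- 87 hospitals x 33 patients, or 218 clinicians x 20-50 reads: about 11-21% at ICC 0.05.

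These rates move by a point or two with the assumed proportion of correct diagnoses. At alpha 0.0083 and ICC 0.05, the simulated size is 0.031 (3.7 times nominal) for 20 reads per clinician and 0.092 (11 times) for 50.

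**Which comparisons are affected**
- Main-effect comparison of levels: as above.
- Factor-by-arm interaction where each clinician is in one arm (Phase IV): the same inflation.
- Factor-by-assistance interaction where every clinician reads with and without the model (Phase III), or records a diagnosis before and after it (Phase V): the shared intercept largely cancels. The simulated size of the unclustered test was 4.5-4.9% at nominal 5%. Inflation would return only if the benefit of assistance itself varied between clusters.

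**The case against.** Section 2.8.3 nowhere says that the regression is ordinary or that diagnoses are treated as independent. The list of adjustments is open-ended, the article is condensed, and random effects or robust variances are often specified in an analysis plan that is not shown. The regression is introduced as confounder adjustment, and subgroup AUCs could be compared with the DBM method. These points stand in part: a reader might infer that the plan commits to independence, and the text does not go that far. What remains is that the section names a particular model and its covariates for factors that vary only between clinicians or hospitals, and omits the correlation that the article addresses elsewhere. DBM is specified for the primary AUC only, and it models readers and cases, not hospitals, so it would not cover tier and region.

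A reader might also infer that false subgroup differences will appear several times too often. The documents do not support that as a general statement. At 348 patients the excess is mild; the larger figures need 87 x 33 = 2,871 patients or, at 50 reads each, 218 x 50 = 10,900 reads, and the article states neither. Against this, 1.6 cases per clinician cannot describe Phase III, because a reader-level AUC needs several severe and non-severe cases per clinician. The true number of reads lies above that average, by an unknown amount.

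Finally, inflation of a main effect does not carry over to a contrast made within clinicians. That stands, and it limits the point as set out in the check.

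**Conclusion.** The point holds in conditional form. If the regression in 2.8.3 is fitted as named, the tests for experience, tier and region exceed their level whenever the ICC is positive and clusters contribute more than one diagnosis. This applies to main-effect comparisons and to Phase IV factor-by-arm interactions. The direction is firm; the size is not. It runs from about 6-7% at nominal 5% with the stated 348 patients over 87 hospitals (ICC 0.05-0.10) to about 11-21% at ICC 0.05 under the larger assumed cluster sizes. All ICCs, the reads per clinician, the 33 patients per hospital and the number of subgroup factors are assumptions. The primary AUC analysis is not touched by this point. It should be corrected because the subgroup results are meant to steer deployment and the change is cheap.

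**What to change.** In section 2.8.3, name the outcome of the regression and specify a mixed-effects logistic model with:
- random intercepts for hospital and for clinician within hospital;
- a crossed case effect where several clinicians read the same case;
- a random assistance effect where assistance varies within clinician (Phases III and V).

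A GEE with cluster-robust variance at hospital level would also serve. Apply Bonferroni to the p-values from that model, with the number of tests stated.

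The cost is a change of wording. No extra patients are needed. Intervals for clinician-, tier- and region-level effects will be wider, which reflects the information that these factors actually carry.
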